## Research questions

1. Acceptability:
   1. What is the overall acceptability of Springfusor use among women with preeclampsia and eclampsia?
   2. What is the acceptability of the springfusor use for magnesium sulphate administration among health providers
   3. What is the level of pain associated with using Springfusor compared to the standard of care in administration of magnesium sulphate?
2. Effectiveness of Springfusor:
   1. What is the discontinuation rate of magnesium sulphate administration using a Springfusor pump compared to standard of care?
3. Safety
   1. What is rate of complications in the two arms?

Hypothesis

Use of Springfusor pump in the administration of magnesium sulphate in women admitted with preeclampsia and eclampsia is more acceptable than the hospital standard practice

Objectives

Primary objective

1. To compare the acceptability of the Springfusor pump to the standard of care in the administration of magnesium sulphate.

Secondary objective

1. To compare the proportion of complications between the Springfusor pump and the standard of care groups
2. To determine level of pain associated with using Springfusor compared to the standard of care?
3. To determine the discontinuation rate of administration of magnesium sulphate among women admitted with preeclampsia and eclampsia
4. To assess the reliability of Springfusor pump in the delivery of magnesium sulphate when used repeatedly
5. To assess the acceptability of the Springfusor pump for the administration of magnesium sulphate among the health providers.

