### Intervention

Women in the intervention arm (Springfusor group) will have their loading and maintenance therapy of magnesium sulphate using IV infusion administered using a Springfusor infusion pump. The loading dose will be 4 gm of 50% magnesium sulphate in 10 ml syringe administered over 20 mins. The maintenance dose of 4 gm of 50% magnesium sulphate in 10 ml will administered over 4 hours. The 4 gm dose will be repeated every 4 hours for 24 hours

Women in the control arm (Standard of care group) will have magnesium sulphate administered according to the standard hospital practice. The loading dose of is administered using an IV-push in which health worker manually and slowly inject 4 gm of 20% Magnesium sulphate in 20 ml syringe over 15-20 minutes. This is immediately followed by IM injection of 10 gm of 50% magnesium sulphate and 1 ml of lignocaine into the gluteal muscles (5 gm on each buttocks). The maintenance dose of 5 gm IM injection every 4 hourly for 24 hours. Over the 24 hour period the intravenous group (intervention) would have got 28 gm of magnesium sulphate while the intramuscular group (control) would have received 39 gms. The higher total dose in the control group is assuming a reduce bioavailability of intramuscular drug.

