- *Feasibility of Springfusor pump use: ⃰* The proportion of women who have a Springfusor used for administration of magnesium sulphate and experience some technical problem with its use, blockage of FCT, the number of attempts made prior to successful Springfusor placement, the number of failed Springfusor placement and the number of FCTs and spilled magnesium sulphate used will also be documented.
- The *reliability** of the Springfusor to administer magnesium sulphate in the prescribed time will assessed for the loading period and the maintenance period. The intra-correlation coefficient for the device will be calculated.

These outcomes will be compared between the women in the two arms. A *outcome will be reported only for women who will have magnesium sulphate administered using Springfusor

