**Data analysis**

Data analysis will be performed by the PI. Descriptive statistics will be used to summarize baseline characteristics of study participants and assess if randomization was successful. The baseline characteristics will too give guidance as to which variables need to be adjusted for in the final analysis.

Acceptability and safety data will be evaluated using intention-to-treat (ITT) analysis. For comparing the maternal health outcome between intervention and control arms, the main analyses will look at the following variables;

1. Proportion of study participants who regarded magnesium sulphate administration using Springfusor or Pritchard route was acceptable. This will be compared using chi-square.
2. *Rate of complications of preeclampsia and its management:* Proportion of preeclamptic and eclamptic women who developed magnesium sulphate toxicity, abnormal liver and renal function test, infection at the injection and maternal deaths
3. The intensity of pain will be analysed using a ttest and presented as means and standard deviation
4. *Feasibility of Springfusor pump use:* The proportion of women who have a Springfusor used for the administration of magnesium sulphate and experience some technical problem with its use, blockage of FCT, the number of attempts made prior to successful Springfusor placement, the number of failed Springfusor placement and the number of FCTs used and spilled magnesium sulphate.
5. *The reliability of the springfusor:* The intra-class correlation coefficient (ICC) will be calculated. The closer the ICC to 1, the higher the reliability, ICC <0.4; the poor the reliability and ICC 0.4-0.75; the fair the reliability.

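### An intraclass correlation cannot show whether the Springfusor delivers in a fixed prescribed time: uniformly accurate pumps would be graded poor, and a bias shared by all pumps would not be seen

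*Protocol*

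**What the plan says.** The fourth secondary objective (Protocol, Research questions) is "To assess the reliability of Springfusor pump in the delivery of magnesium sulphate when used repeatedly".

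Outcome Measures makes this concrete. The reliability "of the Springfusor to administer magnesium sulphate in the prescribed time will assessed for the loading period and the maintenance period", and then "The intra-correlation coefficient for the device will be calculated". A footnote to the starred outcomes, of which reliability is one, limits them: the "outcome will be reported only for women who will have magnesium sulphate administered using Springfusor".

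The prescribed times are in Intervention and are the same for every woman and every use: "The loading dose will be 4 gm of 50% magnesium sulphate in 10 ml syringe administered over 20 mins" and "The maintenance dose of 4 gm of 50% magnesium sulphate in 10 ml will administered over 4 hours".

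Data analysis, item 5, gives the only analysis of this outcome: "The intra-class correlation coefficient (ICC) will be calculated. The closer the ICC to 1, the higher the reliability", followed by the cut-offs "ICC <0.4; the poor the reliability and ICC 0.4-0.75; the fair the reliability". The form of ICC is not given. No deviation from the prescribed time, tolerance or within-device SD is mentioned.

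**The concern.** An ICC suits an instrument that has to tell different subjects apart: true differences between subjects form the numerator, and measurement noise adds to the denominator. Here there are no true differences to detect. Every pump is meant to empty the syringe in the same time, and the better the pumps agree with one another, the smaller the numerator. The prescribed time, which is what the outcome is about, appears nowhere in the formula.

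The Protocol does not leave this open. It fixes the statistic, the direction in which it is read and the cut-offs. A set of interchangeable, accurate pumps could be reported as having poor reliability, and a set of pumps that often miss the target could be reported as highly reliable. Reuse is one of the main arguments made for the device, and the Justification says the results may be used to argue for scale-up, so a wrong grade here would matter beyond the trial.

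**Working it through.** The Protocol reports no figure for this outcome, so there is nothing to reproduce. The check asks what the stated statistic would return for pumps of known behaviour.

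**Inputs from the Protocol.** Target T = 240 min for maintenance and 20 min for loading (Intervention). Graded poor if ICC < 0.4, fair if 0.4 to 0.75, better as it nears 1 (Data analysis, item 5).

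**Assumptions.** The Protocol gives no SDs, so between-pump SD (sb) is taken over 0 to 40 min and within-pump SD (sw) over 0.5 to 40 min. Times are taken as normal. A window of ±10% of target (216 to 264 min) serves only to illustrate accuracy.

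**Formulas.**
- ICC = sb² / (sb² + sw²)
- Total SD s = √(sb² + sw²)
- With mean time equal to T, share within the window = 2Φ(24/s) − 1

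**Two worked cases, both centred on 240 min.**
- sb = 2, sw = 6: ICC = 4/(4 + 36) = 0.10. s = √40 = 6.32; 24/6.32 = 3.79; share = 99.98%.
- sb = 40, sw = 10: ICC = 1600/(1600 + 100) = 0.94. s = √1700 = 41.2; 24/41.2 = 0.58; share = 44%.

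**Range of cases.**

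| Pump behaviour | Mean (min) | sb | sw | ICC | Within ±10% | Grade under item 5 |
|---|---|---|---|---|---|---|
| Uniform and accurate | 240 | 0 | 2 | 0.00 | 100% | poor |
| Nearly uniform, accurate | 240 | 2 | 6 | 0.10 | >99.9% | poor |
| Accurate, tiny stable differences | 240 | 2 | 0.5 | 0.94 | 100% | near 1 |
| Stable large differences | 240 | 40 | 10 | 0.94 | 44% | near 1 |
| Different and erratic | 240 | 40 | 40 | 0.50 | 33% | fair |
| Erratic from use to use | 240 | 0 | 40 | 0.00 | 45% | poor |
| All pumps 60 min late | 300 | 0 | 2 | 0.00 | 0% | poor |

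The first and last rows have the same ICC, with all infusions on target in one and none in the other. The third and fourth rows also share an ICC, with 100% and 44% on target.

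Simulation of the one-way ANOVA ICC, with 20 pumps × 12 uses and 10 pumps × 24 uses, gave the same pattern in the scenarios run. For uniform accurate pumps, 95% of runs with 20 pumps lay between −0.05 and 0.06.

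**Loading period.** The ICC has no units. Dividing the target and every SD by 12 (240/12 = 20) leaves each ICC and each share unchanged, so the same holds for the 20-minute dose.

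**Other forms of ICC.** An agreement ICC of measured against prescribed time, maintenance only with an error SD of 2 min, is also 0.00, because the prescribed time does not vary. Pooling loading and maintenance gives about 0.96 even with a 20% timing error, simply because 20 and 240 are far apart.

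**The case against.** The strongest defence is that the objective concerns repeated use, and for a given between-pump SD a pump that repeats itself more closely does score higher. Pumps that are erratic from use to use, or that all run late, score about 0 and would be graded poor, which is the right verdict. This stands, and it limits the point. A reader might infer that the ICC simply runs backwards, or that any inconsistent or biased set of pumps scores near 1. The calculations do not support that: only stable differences between pumps push the ICC towards 1, use-to-use variation lowers it, and a shared bias does not move it. The right grade for late or erratic pumps is also no evidence that the statistic works, since accurate uniform pumps receive the same grade.

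A reader might also infer that blocked or failed infusions are lost, because timing runs to completion of the syringe and the outcome covers only women given the drug by Springfusor. The Protocol records tube blockage, technical problems and failed placements under feasibility, and stopped treatment under discontinuation. They are absent from the timing statistic, not from the trial. The footnote can be read as saying no more than that the starred outcomes apply to one arm.

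Finally, all the SDs are assumed, and this is the fourth of five secondary objectives. Both remarks are fair. The first does not affect the main conclusion, because the target is missing from the formula whatever the SDs are.

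**Conclusion.** The point holds in this form: the stated ICC is uninformative about delivery in a fixed prescribed time, and its cut-offs can give the wrong grade. Accurate, interchangeable pumps are graded poor (ICC 0.10 with over 99.9% within 10% of target at SDs of 2 and 6 min). Pumps with stable differences score near 1 (0.94 with about 44% within 10% at SDs of 40 and 10 min). A bias shared by all pumps is invisible. The sizes rest on assumed SDs, normal times and an illustrative 10% window; the direction rests only on the definition of the ICC and the constant targets.

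The defect lies in what the Protocol fixes, not in detail left to an analysis plan. It should be corrected before analysis, but it is not critical to the trial: the outcome is secondary and descriptive within the Springfusor arm, and the primary acceptability comparison is unaffected.

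**What to change.** In Data analysis, item 5, and in the matching sentence of Outcome Measures, remove the ICC and its cut-offs. Report the following for loading and maintenance separately:

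- **Accuracy:** mean deviation from the prescribed time with a 95% confidence interval.
- **Consistency and drift:** between-pump and within-pump SD from a mixed model with pump as random effect and use number as covariate. State that the within-pump SD includes variation between flow control tubes, which set the flow rate and are replaced after each use.
- **Success:** the proportion of started infusions that finish within a window fixed in advance. Device failures such as blockage count as failures; stops by the woman's choice or a clinician's decision do not.

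The cost is analysis wording plus one added data item. Loading and maintenance times are already to be measured, and an accountability log tracks the devices. The Protocol does not say that the log links a pump to each infusion, so the pump number should be recorded on the case record form every time.

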# Safety and monitoring

The following mechanisms will be employed to ensure the data quality and integrity of the study. An independent data and safety monitoring board (DSMB) will be established to review the data and make recommendations to investigators concerning study continuation and study modification. The main purpose of the DSMB is to ensure that the study participants are not exposed to undue risk. The DMSB will be called upon to review reported serious adverse events and provide advice on management of the study with relation to risk, and will help assure the continued scientific validity and merit of the study. An interim analysis will be conducted in the study when 2/3 of participants have been recruited. Based on the analysis and if deemed necessary, the DSMB will be asked to provide recommendations on study modification. All data analyzed by the DSMB will be reviewed in strict confidence.

The DSMB will consist of three professionals whose combined experience covers the fields of obstetrics and gynaecology, preeclampsia and eclampsia, biostatistics, and ethical conduct of human subject research. Qualifications for selection include: 1) Expertise in the fields of interest, 2) Experience in conduct of clinical trials and statistical knowledge, 3) independence from the direct management of the clinical trial, 4) no financial, scientific or other conflict of interest. Signed conflict of interest statements from each board member must be on the file at PI office prior to initiating DSMB activities.

Accountability log will be used to track the use of Springfusor devices and FCTs during the study. The product will be stored in accordance with the requirements of Springfusor. Any unused Springfusor and FCTs will be held at Mulago Hospital until final instructions are received from Go Medical Ltd.

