### Randomisation

A biostatistician at the Clinical Epidemiology Unit of Makerere University College of Health Sciences and not involved in the clinical trial will develop allocation sequence using an online computer random number generator in different block sizes. Women with preeclampsia and eclampsia will be randomized to have their magnesium sulphate administered with Springfusor pump or the hospital standard of care. The study participants will be randomized only after they have qualified for the study and signed informed consent. Serially numbered sealed opaque envelopes (concealed allocation) containing the randomization group will be provided at site in a secure place within the ward. Trained research staff will open the envelope to determine the group assignment after the participant is enrolled, completed all the baseline assessment and it is time to allocate the intervention

Blinding: Because of the nature of the study, it is difficult to blind the study, the implementation of the allocation and measurement of the outcome.

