#### Stopping rules

#### Stopping will be implemented if the use of the Springfusor for administration of magnesium sulphate becomes a national policy or if at the interim review, the acceptability of the Springfusor for the administration of magnesium sulphate is superior than the standard of care or, there significant complications in the Springfusor arm. However, during the accrual of the study, when the cases experiencing respiratory depression due to magnesium sulphate toxicity in the Springfusor arm exceeds 12.5%, an emergency DSMB meeting will be called to review if the study is to stop.

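### As the protocol is written, interim acceptability by arm is not kept from the team that is still collecting that outcome

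*Protocol*

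**What the plan says.** - **Who analyses.** Protocol, Data analysis: "Data analysis will be performed by the PI". Interim and final analysis are not separated, and no other analyst is named. The only statistician given a task is the one under Randomisation, described as "not involved in the clinical trial will develop allocation sequence".
- **When the interim happens.** Protocol, Safety and monitoring: "An interim analysis will be conducted in the study when 2/3 of participants have been recruited". The sentence does not say who conducts it.
- **What the DSMB does at the interim.** The next sentence reads "Based on the analysis and if deemed necessary, the DSMB will be asked to provide recommendations on study modification". It does not say who judges the necessity.
- **What the DSMB does in general.** Earlier in that section, the independent board "will be established to review the data and make recommendations to investigators concerning study continuation and study modification". No condition is attached.
- **Confidentiality.** "All data analyzed by the DSMB will be reviewed in strict confidence". This covers the board's own review and nothing before it.
- **What the interim can trigger.** Protocol, Stopping rules: the trial may stop "if at the interim review, the acceptability of the Springfusor for the administration of magnesium sulphate is superior than the standard of care". No decision-maker is given. For excess respiratory depression in the Springfusor arm, by contrast, "an emergency DSMB meeting will be called to review if the study is to stop".
- **How the outcome is collected.** The trial is open label, and Randomisation says that measurement of the outcome is also difficult to blind. Under Study procedure and Outcome Measures, acceptability is a five-point Likert rating that study staff obtain in an interview before discharge. Women who stop by choice or because of side effects are counted as finding the method unacceptable.

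**The concern.** The interim criterion rests on the primary outcome, so the look has to compare acceptability between arms. The only analyst the protocol names is the PI, and the board is approached after the analysis and on a condition. Nothing in the text keeps the by-arm result from the people running the trial.

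This matters more here than it would for a hard endpoint. The outcome is a rating given to staff who know the arm. The reason recorded for a stop also counts: a stop by choice or for side effects makes the woman a failure on the primary outcome, whereas a health worker's decision is listed only under the secondary discontinuation outcome. Under Data quality assurance, the PI reviews the case record forms and gives feedback at study meetings, so there is a possible route from interim knowledge to the data collectors. At stake are the comparability of ratings before and after the look, and the credibility of any early stop for superior acceptability.

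**Working it through.** **1. The plan's own figure.** Inputs from Sample size: control acceptability 31%, 50% more acceptable with Springfusor (read as relative), power 90%, alpha 0.05 (taken as two-sided).

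- Springfusor: 0.31 × 1.5 = 0.465. Design effect: 46.5 − 31 = 15.5 points.
- Mean proportion: (0.31 + 0.465)/2 = 0.3875.
- n = [1.960 × √(2 × 0.3875 × 0.6125) + 1.2816 × √(0.31 × 0.69 + 0.465 × 0.535)]² / 0.155² = (1.350 + 0.872)² / 0.0240 ≈ 205.5, so 206 per arm.
- With continuity correction: (205.5/4) × [1 + √(1 + 4/(205.5 × 0.155))]² ≈ 218.2, so 219 per arm. This matches the protocol.
- 219 × 1.10 ≈ 241 per arm, 482 in all.

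The reading of 15.5 points as the design effect is therefore the protocol's own. The point itself does not depend on the sample size being right.

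**2. Position of the look.** 482 × 2/3 = 321.3, about 321 women recruited. 482 − 321 = 161 are still to come, one third of the trial. If the trial continues, these 161 are rated after the look. Women recruited but not yet discharged would add slightly to that number.

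**3. The statements side by side.**

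| Question | What the protocol states |
|---|---|
| Who does the analysis? | The PI, with no exception for the interim |
| Who runs the interim? | Not stated |
| Does the DSMB get the interim? | General remit: it reviews the data, unconditionally. Interim sentence: asked for recommendations afterwards, if someone judges it necessary |
| Who applies the acceptability criterion? | Not stated |
| Who deals with the respiratory depression trigger? | The DSMB |
| What is confidential? | Data analysed by the DSMB |

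The third row is a conflict: a board that always reviews data and advises on continuation cannot also be one whose input at the only planned interim is optional. The other rows show that no barrier is described between the interim result and the trial team.

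**4. Illustrative size.** The documents give no figure for how far knowledge of the interim might move ratings, so this is an assumption with a range. If the Springfusor acceptability rate shifts by s points in the last third only and the control rate does not move, the final difference moves by s × 1/3:

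| Assumed s (points) | Shift in final difference (points) | Share of 15.5 points |
|---|---|---|
| 2 | 0.7 | 4% |
| 5 | 1.7 | 11% |
| 10 | 3.3 | 22% |

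The result is linear in s and says nothing about which s is plausible.

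**The case against.** The strongest reply is that the protocol nowhere says the PI runs the interim. The sentence assigning analysis to the PI opens a section about baseline tables and the main and final analyses, and the interim is not mentioned there. The interim sentence is in the passive voice. The conditional sentence concerns study modification and could mean that the board is asked if a modification is needed, not that it is otherwise left uninformed. The board is independent, has biostatistics expertise and has an unconditional remit. Operational detail on interim reports often sits in an SAP or a DSMB charter, which are not shown here.

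Much of this stands, and it limits what can be claimed:

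- A reader might infer that investigators will see and act on interim acceptability. The text permits this but does not state it.
- A reader might infer that the board is consulted only at the investigators' discretion. The general remit in the same section says otherwise, so the fair description is a conflict.
- A reader might infer that parties with an interest in the result decide on stopping. Stopping rules names no one for that criterion, and the investigators declare no conflict of interest.
- Bias would also require results to pass from the analyst to the interviewers. The PI's meetings with staff make that possible, but no text says that results would be shared.
- Interviewers already know the arm, so some open-label bias exists whatever is done about the interim.

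What does not stand is that this is only missing detail. The protocol assigns the analysis without exception, places the interim before a conditional request to the board, and contradicts that condition in the same section. An SAP or charter that said otherwise would still have to override these sentences.

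**Conclusion.** The point holds in a limited form. As written, the protocol does not protect interim acceptability by arm from the team conducting an open-label trial, while a subjective primary outcome is still to be collected by study staff in about 161 of 482 women. Its statements on the DSMB's part in the interim conflict, and nobody is assigned to apply the acceptability stopping criterion.

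The size of any bias is unknown. The range of 0.7 to 3.3 points rests wholly on an assumed shift of 2 to 10 points in one arm in the last third, on the trial continuing past the look, and on results reaching the interviewers. It should not be quoted as an expected bias. The point is worth acting on because the repair is cheap and removes an avoidable route to bias.

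**What to change.** Reword Data analysis, Safety and monitoring, and Stopping rules so that they agree:

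1. The PI's analysis role covers the final analysis only.
2. The interim comparison by arm is prepared by the DSMB's biostatistics member or another statistician outside trial conduct. If the biostatistician who makes the allocation sequence were chosen, the description of that role would have to change.
3. The interim comparison always goes to the DSMB; delete the necessity condition.
4. The DSMB makes the recommendation under the interim acceptability criterion.
5. The PI and study staff receive only the recommendation (continue, modify or stop) until data collection ends, and the confidentiality sentence is extended to cover preparation of the interim report.

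The cost is one interim data transfer and a small amount of statistician time. Sample size, outcomes and clinical care are unchanged. The change does not remove the bias that comes from open-label outcome measurement itself.
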